### Study outcomes

2.5

The primary endpoint of this study is the mean AHI measured 6 months post-intervention. This time point was selected because it reflects the earliest clinically relevant assessment at which treatment effects are expected to be stable in both arms: after postoperative recovery following TORS and after establishment of CPAP/MAD use and adherence. The PG will be performed at baseline, 6 months and 12 months. A lower AHI reflects improved airway patency and is thus clinically meaningful in assessing treatment effectiveness between groups. Twelve month follow up is included as an important secondary endpoint to evaluate durability of treatment effects in this chronic condition. Secondary outcomes include: (1) 50% reduction of AHI at 6 months compared to baseline and or AHI below 20/h (Sher's criteria) [2,21] reduction of AHI at 12 months to <5/h will be defined as surgical cure [3,22] differences in mean ODI 4% values at 6 months and 12 months, and reduction of ODI 4% to 25% relative to baseline will be defined as clinically relevant [4,22] differences between FOSQ-35 [15] scores at 3 months, 6 months and 12 months in which an increase of 10% of the score compared to baseline on the FOSQ-35 questionnaire will be defined as clinically relevant [5,22] differences between scores of ESS at 3 months, 6 months and 12 months and a reduction on the ESS to <10 will be defined as clinically relevant [6,23] differences between scores of quality of life questionnaires EQ-5D-5L [19] at 3 months, 6 months and 12 months [7]; differences in scores on the visual analogue scales (VAS) for snoring, tiredness and globus in all patients between baseline, 3, 6 and 12 months [8]; VAS scores swallowing and taste for patients in the TORS group at baseline compared to 3 months, 6 months and 12 months.

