### Statistical analysis

2.10

All statistical analyses will be conducted using IBM SPSS Statistics. The full analysis set (FAS) follows the Intention-To-Treat (ITT) principle and includes all planned subjects, except those with major protocol violations, no post-baseline data, or no study intervention.

Baseline characteristics, including age, gender, BMI, PG, ENT exam, DISE results, smoking, and reflux history, will be summarized using descriptive statistics. Quantitative variables will be presented as mean and standard deviation or as median with interquartile range or minimum/maximum, and qualitative data as frequencies and percentages, with 95% confidence intervals where applicable. Data normality will be assessed graphically and numerically. No formal statistical tests will be performed for baseline comparisons. The primary outcome (AHI at 6 months) will be analysed using independent *t*-test or Mann-Whitney *U* test depending on data distribution. Given the RCT design, adjustments for baseline differences are not foreseen. In case of missing data this will be mentioned in the results. Missing data will not be replaced. For all hypothesis testing, a two-sided p-value of less than 0.05 indicates statistical significance. Secondary outcomes will follow the same approach. For continuous variables, appropriate group comparisons (*t*-test, Mann–Whitney U, ANOVA, or Kruskal–Wallis) will be used. For categorical outcomes, Fisher's exact or Chi-square tests will be applied as applicable. Because the control arm includes two standard non-surgical modalities (CPAP and MAD), additional prespecified analyses will be performed to assess robustness. These include [1] subgroup analyses comparing TORS vs CPAP and TORS vs MAD separately (exploratory due to sample size) and [2] sensitivity analyses adjusting for control modality (CPAP vs MAD) when evaluating the primary endpoint. Treatment adherence data will be reported descriptively and considered when interpreting outcomes. Other study parameters will be analysed descriptively as outlined above.

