## Discussion

3

The proposed study aims to evaluate the efficacy of TORS compared with standard non-surgical therapies for OSA. By assessing both clinical effectiveness and long-term patient outcomes, this study will provide insights into the optimal OSA treatment strategy and evaluate whether surgical intervention should be positioned earlier in the treatment pathyway or remain a secondary option in clinical guidelines. Given the chronic nature of OSA, 12-month outcomes will be used to evaluate durability of treatment effects and to support interpretation beyond the primary 6-month endpoint.

A limitation of this pragmatic study design is that the control arm includes two distinct conservative modalities (CPAP and MAD), which may introduce within-arm heterogeneity. Therefore, subgroup and sensitivity analyses by control modality are planned to assess the consistency of the primary findings. Another limitation of this trial is the relatively small sample size, which may reduce statistical power to detect modest differences between groups, particularly for secondary outcomes and repeated measures analyses, increasing the risk of type II error. Therefore, results will be interpreted with emphasis on effect estimates and confidence intervals rather than statistical significance alone, and non-significant findings will be interpreted cautiously.

Importantly, outcomes of upper airway surgery depend on careful patient selection and individualized treatment planning. DISE can support this process by identifying the relevant anatomical levels and patters of collapse, enabling more targeted surgical decision-making and potentially optimizing outcomes [27,28]. In addition, while PG outcomes such as AHI remain important objective markers of disease severity, they do not fully capture treatment benefit from the patient perspective. Therefore, quality of life daytime sleepiness, and functional outcomes should be considered key endpoint when evaluating surgical versus non-surgical treatment strategies, particularly given their relevance to long-term adherence, acceptance and overall patient benefit [29].

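### Swallowing and taste VAS in the TORS arm is a before-after comparison in the same patients, but section 2.10 gives it tests for independent groups and no paired option

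*Protocol article*

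**What the plan says.** Section 2.5 (Study outcomes) of the protocol article defines the last secondary outcome, number 8, as "VAS scores swallowing and taste for patients in the TORS group at baseline compared to 3 months, 6 months and 12 months". Only one arm contributes, and each patient is measured up to four times.

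Outcome 7 is worded as "differences in scores on the visual analogue scales (VAS) for snoring, tiredness and globus in all patients between baseline, 3, 6 and 12 months". This can be read as a comparison of visits or of arms.

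Section 2.10 (Statistical analysis) sets the primary test: "The primary outcome (AHI at 6 months) will be analysed using independent *t*-test or Mann-Whitney *U* test depending on data distribution". It continues: "Secondary outcomes will follow the same approach. For continuous variables, appropriate group comparisons (*t*-test, Mann–Whitney U, ANOVA, or Kruskal–Wallis) will be used". The threshold is general: "For all hypothesis testing, a two-sided p-value of less than 0.05 indicates statistical significance". Section 2.10 names no paired test, signed-rank test, Friedman test or mixed model.

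The Discussion, in describing limited power, speaks of reduced power "particularly for secondary outcomes and repeated measures analyses". Section 2.10 describes no analysis of that kind.

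**The concern.** For outcome 8 the question is whether the same patients changed after surgery. An independent-sample test asks whether separate groups of patients share one distribution or mean. With no second arm, the listed tests can be applied only by letting each visit stand in for a group. That ignores the correlation between a patient's own scores. When the correlation is positive, as is usual for repeated ratings by one person, the standard error of the change is too large. The interval is then too wide and the test rejects too rarely.

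The direction of the error matters here. The Introduction names dysphagia among the risks of TORS that the non-surgical treatments do not carry, and outcome 8 is the listed secondary outcome on swallowing and taste. An insensitive test makes a finding of no significant change more likely even if patients have worsened.

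**Working it through.** **Inputs from the documents.** There are 25 patients per arm, or 21 after allowance for missing data (section 2.8). The two-sided level is 0.05 (section 2.10). Outcome 8 is compared at baseline, 3, 6 and 12 months in TORS patients (section 2.5).

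**Assumptions, not in the documents.** Scores are normal with equal SDs at the visits compared, the within-patient correlation r is 0.3, 0.5 or 0.7, and the true change is 0.5 SD.

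**The plan's own figure.** No power is stated for outcome 8. The only stated power is 82% for the primary comparison (21 per arm, difference 10.0, SDs 10.0 and 12.0). With SE = √(100/21 + 144/21) = 3.41 and a non-central t distribution on 40 df, it reproduces as 81.7%. That calculation compares two arms and is not affected by this point.

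**Step 1: standard error of the change, in SD units.**
- Independent formula: √(2/n). For n = 25: √(2/25) = 0.283, whatever r is.
- Correct (paired) formula: √(2(1−r)/n). For n = 25: 0.237 (r = 0.3), 0.200 (r = 0.5), 0.155 (r = 0.7).
- Ratio: 1/√(1−r) = 1.20, 1.41, 1.83.

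**Step 2: width of the 95% interval.** The independent test uses t on 48 df (2.011) and the paired test t on 24 df (2.064). The factor 2.011/2.064 = 0.974 trims the ratios slightly, to 1.16, 1.38 and 1.78. Intervals are thus about 1.2 to 1.8 times too wide.

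**Step 3: actual error rate of the independent t-test.** The large-sample formula 2 × P(Z > 1.96/√(1−r)) gives 1.9%, 0.6% and 0.03%. Simulation at n = 25 (100,000 runs per setting) gives 2.1%, 0.7% and 0.1%. The paired t-test holds 5.0% in the same runs.

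**Step 4: power for a 0.5-SD change, baseline against one later visit.** The t-test rows come from the same simulation, and the rank-test row from 20,000 runs.

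| Comparison | r = 0.3 | r = 0.5 | r = 0.7 |
|---|---|---|---|
| Independent t vs paired t, n = 25 | 39% vs 53% | 38% vs 67% | 35% vs 87% |
| Independent t vs paired t, n = 21 | 33% vs 46% | 30% vs 59% | 27% vs 80% |
| Mann-Whitney vs signed-rank, n = 25 | 37% vs 51% | 35% vs 64% | 32% vs 85% |

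The non-central t distribution confirms the paired-t figures at n = 25: 52.7%, 67.0% and 87.2%. At r = 0 the loss vanishes (41% vs 39%).

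**Step 5: all four visits together**, n = 25, every follow-up visit shifted by 0.5 SD, equal correlation between visits (40,000 runs). At r = 0.5, one-way ANOVA has an error rate of 0.2% and power of 27%, against 5.2% and 71% for repeated-measures ANOVA. At r = 0.7, power is 20% against 92%.

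**The case against.** The strongest reply is that section 2.10 does not assign an independent test to outcome 8. The word independent is attached only to the primary t-test. In the secondary list, t-test and ANOVA are unqualified and the comparisons are called appropriate. ANOVA and Kruskal-Wallis also have an obvious use across TORS, CPAP and MAD. A sentence about group comparisons may simply not reach a one-arm outcome, and the Discussion's mention of repeated measures suggests that such analyses are intended. The gap would then be detail left to a fuller document.

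This stands only in part. The sentence before the list places secondary outcomes, without exception, under the primary's approach. The word appropriate qualifies group comparisons and does not bring in methods of another kind. Even if t-test and ANOVA are read as paired or repeated-measures, the planned switch for non-normal data leads to Mann-Whitney or Kruskal-Wallis, which have no paired form.

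Other points against a stronger reading do stand:
- A reader might infer that snoring, tiredness and globus are equally affected. The words on all patients in outcome 7 may only say who completes the scale. A comparison of arms at each visit, or of change scores, is a natural reading, and independent tests would then be valid.
- A reader might infer that MDADI and SWAL-QoL are affected too. They are other study parameters, which section 2.10 analyses descriptively.
- A reader might fear excess false positives from pooling several visits as independent values. No section proposes pooling, and the error shown here is conservative.
- Swallowing does not rest on this VAS alone. The speech language pathologist's evaluations and the recording of undesirable experiences also cover it.
- Secondary outcomes are exploratory, and the Discussion promises emphasis on intervals and caution with non-significant results. That softens the consequence but does not remove it, because the intervals are too wide by the same mechanism.

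**Conclusion.** The point holds for outcome 8. The rule in section 2.10, followed literally, does not fit the comparison defined in section 2.5. With 25 patients and r between 0.3 and 0.7, intervals are about 1.2 to 1.8 times too wide, the actual error rate is about 2% to 0.1%, and power for a 0.5-SD change falls by roughly 13 to 52 percentage points. These sizes rest on an assumed correlation, effect, normality and equal SDs, and a bounded VAS may depart from the last two. They do not support saying that deterioration will be missed, only that it is more likely to be. For outcome 7 the documents support no more than a request to say what is compared. The primary analysis, the sample size and the between-arm comparisons are unaffected. The correction should be made because it is nearly free and the outcome concerns possible harm from surgery.

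**What to change.** In section 2.10:

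1. Exempt outcome 8 from the rule that secondary outcomes follow the primary's approach. Analyse change from baseline at 3, 6 and 12 months with a paired t-test or, for non-normal changes, a Wilcoxon signed-rank test. A linear mixed model with visit as fixed effect and patient as random effect is an alternative. Report the change at each visit with its paired 95% confidence interval.
2. Reserve the independent-sample tests for comparisons between arms.
3. For outcome 7, state whether arms or visits are compared, and use the paired or mixed-model method only if visits are compared.

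The cost is one or two sentences. No further data or patients are needed, and SPSS offers these methods. The small downside is that a paired test drops any patient who lacks one of the two values, which the mixed model largely avoids.

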### Monitoring

2.11

Although no independent Data Monitoring Committee (DMC) has been established for this study due to the relatively small sample size, the low-risk nature of the interventions (surgical and non-invasive standard therapies), and the short-term primary outcomes, all serious adverse events will be assessed by the principal investigator and study team in accordance with institutional and ethical guidelines.

In accordance with Article 10.4 of the Dutch Medical Research Involving Human Subjects Act (WMO), the study will be suspended if there is reason to believe that continuation may endanger participant health or safety. The sponsor will promptly notify the accredited METC, including the reason. The study may only resume after a positive decision by the METC. Participants will be informed by the investigator. All undesirable experiences occurring during the study, whether related to the intervention or not, will be recorded if reported by the subject or observed by the study team. SAEs include death, life-threatening situations, hospitalization or its prolongation, or lasting disability. Events that did not result in these outcomes but could have, based on medical judgement, are also considered SAEs. Elective hospital admissions are not classified as SAEs. Any SAE occurring at Frisius Medical Center Leeuwarden must be reported to the principal investigator within 24 h.

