## Introduction

1

In obstructive sleep apnea (OSA) syndrome, repetitive partial or complete collapse of the upper airway during sleep leads to nocturnal hypoxia and interruption leading to daytime sleepiness [1]. OSA is associated with an increased risk of comorbidities such as hypertension, type 2 diabetes mellitus, and cardiovascular disease [2,3]. The gold standard treatment for OSA is continuous positive airway pressure (CPAP). CPAP effectively reduces apnea hypopnea index (AHI), improves sleep quality and decreases cardiovascular co-morbidities [4,5]. Regardless of the benefits, 30% of patients refuse treatment with CPAP due to several reasons including pressure effect of the mask [4] [[5], [6], [7]]. Another challenge of CPAP is treatment adherence, which requires a minimum usage of 4 h per night on at least 70% of nights. A study by Koehler et al. has shown that after 3 months adherence rates were 54% [8]. Mandibular advancement devices (MADs) are another non-surgical treatment modality that effectively reduce AHI [9], though they are less effective than CPAP. However, MADs demonstrate higher treatment adherence compared to CPAP [10].

For OSA patients who are unable to tolerate CPAP or MADs and are eligible for surgery, transoral robotic surgery (TORS) has emerged as an effective treatment option. TORS focuses on the obstruction at BOT, permanently enlarging the upper airway by removing lingual tonsil tissue. However, like all surgeries, TORS carries inherent risks such as postoperative bleeding, stenosis, infection and dysphagia, all risks that non-surgical therapies do not present. While studies have shown that TORS effectively reduces AHI [11,12], randomized trials comparing its efficacy to standard non-surgical therapies are lacking.

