In this proposed study, a trial designed to address a clinically pragmatic question: whether TORS, an accepted surgical treatment for selected patients but typically positioned after non-surgical therapies in the routine care pathway, provides outcomes that are equal or superior to standard non-surgical management. In this parallel-group, randomized controlled trial with a 1:1 allocation ratio, we will compare TORS to non-surgical therapy (CPAP or MADs). Following a superiority framework, it aims to determine whether TORS provides better sleep outcomes, long-term efficacy, and quality of life while assessing complications, compliance, and functional outcomes. These comparators were chosen because CPAP and MADs are well-established, non-invasive treatments recommended in clinical guidelines and are typically chosen as first options in routine care. Historically, surgery has been considered a last resort in the management of OSA. Therefore, CPAP and MAD are pooled as non-surgical therapy in this trial to reflect real-world conventional management rather than to compare TORS against a single treatment modality. The primary objective of this study is to quantify the effectiveness of TORS relative to CPAP or MADs in treating OSA. Additionally, this study aims to determine the long-term outcomes of TORS compared to conventional therapy, assess functional sleep outcomes in patients undergoing TORS. Furthermore, it will evaluate health-related quality of life in both treatment groups and examine patient compliance with non-surgical therapy. By addressing these objectives, this study aims to provide comprehensive insight into the role of TORS as a treatment modality for OSA, helping to inform clinical decision-making and improve patient outcomes.

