After inclusion and randomization, group 1 will undergo TORS and will be hospitalized post-surgery, which is expected to be 3 days. Patient will be discharged home with pain medication and will visit the outpatient clinic after 6 weeks for evaluation of surgical wounds. Group 2 will be assessed by either a pulmonologist or a MFO surgeon. They will have an evaluation of treatment after 3 months. Time point 0 (T0) starts when patient undergoes surgery and the first day of usage of CPAP or MAD. The TORS group will complete questionnaires at 3, 6 and 12 months and will undergo PG at 6 and 12 months for evaluation of the treatment. Then, they will also have evaluation of swallowing quality of the speech language pathologist at baseline, 2 days after surgery (while hospitalized) and 6 weeks. The CPAP or MAD group will have outpatient follow-ups at the pulmonologist or MFO surgeon at the same time points. Then, they will also complete the questionnaires (3,6 and 12 months) and will undergo PG at 6 and 12 months. The CPAP will be read out at 3,6, and 12 months. For the TORS group, in addition to standards PG and quality of life questionnaires, pain scores using VAS will be recorded. The length of hospital stay will also be monitored.

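### Complications are a stated aim but not a listed outcome, and events are captured passively under unequal scheduled contact, so any comparison of harm is at risk of ascertainment bias

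*Protocol article*

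**What the plan says.** - **Aim.** The Introduction sets out to compare sleep outcomes, long-term efficacy and "quality of life while assessing complications, compliance, and functional outcomes".
- **Expected harms.** The Introduction also states that "TORS carries inherent risks such as postoperative bleeding, stenosis, infection and dysphagia".
- **Outcomes.** Section 2.5 lists the primary, secondary and other parameters. It goes down to dentition, reflux and snoring time, but has no complication or adverse-event outcome. Section 2.10 describes no analysis of complications.
- **Capture of events.** Section 2.11 covers "All undesirable experiences occurring during the study, whether related to the intervention or not" and says that these "will be recorded if reported by the subject or observed by the study team". On serious events it adds: "Any SAE occurring at Frisius Medical Center Leeuwarden must be reported to the principal investigator within 24 h".
- **Contact, TORS arm.** Sections 2.3 and 2.6 give a 3-day stay. Section 2.6 adds speech-language evaluation at baseline, day 2 and week 6, and says that the patient "will visit the outpatient clinic after 6 weeks for evaluation of surgical wounds". After that it names questionnaires at 3, 6 and 12 months and polygraphy at 6 and 12 months.
- **Contact, control arm.** Section 2.6 gives an evaluation after 3 months, and then: "The CPAP or MAD group will have outpatient follow-ups at the pulmonologist or MFO surgeon at the same time points". Section 2.3 adds telephone and in-person contact as needed for technical or adherence problems.
- **Blinding.** Section 2.9 says that neither patients nor investigators can be blinded.

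**The concern.** The Discussion says that the trial should help decide whether surgery belongs earlier in the treatment pathway. That question turns on harm as well as on AHI. The article announces that complications will be assessed, prints its outcome list, and leaves most of the named complications off it.

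What remains is the general adverse-event rule, under which an event enters the data if the patient mentions it or the team happens to see it. In an open trial both can depend on the arm: on what patients have been told to expect, and on how often a clinician sees them. If the arms are then set side by side on recorded events, part of any difference may reflect the chance of being recorded and not the chance of having an event. Events that nobody asked about cannot be reliably recovered after the trial.

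**Working it through.** The plan states no figure on harm, so there is none to reproduce. The check sets the sections side by side and then shows how much unequal capture could matter.

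**1. Which harms have a listed measure, and in which arm (sections 2.3, 2.5, 2.6, 2.11)**

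| Harm | TORS | Control |
|---|---|---|
| Bleeding, stenosis, infection | none listed | none listed |
| Re-operation | none listed | none listed |
| Dysphagia | VAS swallowing, MDADI and SWAL-QoL at baseline, 3, 6 and 12 months; speech-language evaluation at baseline, day 2 and week 6 | none listed |
| Taste | VAS at baseline, 3, 6 and 12 months | none listed |
| Pain | VAS | none listed |
| Globus | VAS | VAS |
| Unplanned hospitalisation | serious adverse event, not an outcome | serious adverse event, not an outcome |
| Device side effects | not applicable | counselling only, no measure listed |

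Of the four risks that the Introduction names, one (dysphagia) is measured actively, and in one arm only. Globus is the only symptom of this kind with a value in both arms.

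**2. Scheduled contact by arm (sections 2.3, 2.6)**

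| Time from T0 | TORS | Control |
|---|---|---|
| Days 0 to 3 | inpatient stay, day-2 evaluation | none clearly dated |
| Week 6 | outpatient visit, speech-language evaluation | none clearly dated |
| Month 3 | questionnaires | evaluation of treatment, questionnaires, CPAP read-out |
| Months 6 and 12 | questionnaires, polygraphy | questionnaires, polygraphy, CPAP read-out |

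The sentence on control outpatient follow-up does not say which time points it means. It can be read in three ways:

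- as months 3, 6 and 12, the most natural reading;
- as the speech-language times in the sentence just before it;
- as saying that TORS patients also have clinic visits at those times.

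On the first reading, chances of capture are greater in TORS up to week 6 and greater in control from month 3.

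**3. What one missed patient is worth**

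The planned size is 25 per arm (section 2.8).

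- One patient is 1/25 = 4 percentage points.
- With 0 recorded events in 25, the exact two-sided 95% upper limit is 1 − 0.025^(1/25) = 13.7%.

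One or two missed patients therefore change the picture.

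**4. Illustration of unequal capture**

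The true risk and the capture probabilities here are assumptions; the document gives neither. Take a true risk of 20% in both arms, so 25 × 0.20 = 5 true events per arm.

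| Capture TORS / control | Expected recorded events | Apparent risk ratio |
|---|---|---|
| 90% / 90% | 4.5 / 4.5 | 1.00 |
| 90% / 70% | 4.5 / 3.5 | 0.90/0.70 = 1.29 |
| 90% / 50% | 4.5 / 2.5 | 0.90/0.50 = 1.80 |
| 70% / 90% | 3.5 / 4.5 | 0.70/0.90 = 0.78 |

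The ratio depends only on the two capture probabilities, not on the assumed risk. With no true difference, it can fall on either side of 1.

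**The case against.** There is a serious case on the other side.

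- **Harm is not ignored.** Swallowing is measured repeatedly, and pain, taste, globus and length of stay are recorded. Hospitalisation and its prolongation count as serious adverse events, so unplanned re-admission already has a route. This stands, and it narrows the gap to bleeding, stenosis, infection, re-operation and device side effects. It does not close it, because nearly all the symptom measures are confined to TORS.
- **The recording rule is the same in both arms and covers related and unrelated events.** This is true, but one rule gives equal capture only if the chances to report and observe are alike.
- **No formal comparison of harm is specified.** The article calls the surgical risks ones that non-surgical treatment does not carry, so describing each arm separately is reasonable. This stands against calling the comparison biased as a fact. It is also why each type of complication should be shown separately and not only in a pooled total.
- **This is a condensed article.** Checklists and case-report-form prompts may sit in the full protocol. So the lack of a printed checklist is not the point. The point is that the aim and the printed outcome list do not match, and that the capture rule as stated is passive.

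A reader might go further and infer that late surgical complications will be undercounted, so that the comparison leans towards TORS, with no clinician contact for TORS after week 6 against three for control. The document does not support this. That count starts only after the surgical visits, leaving out the period when TORS has more contact. It also rests on one reading of an ambiguous sentence, and on taking silence about TORS clinic visits as proof that there are none. TORS patients still have questionnaires at 3, 6 and 12 months and polygraphy at 6 and 12 months, when an event could be reported.

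**Conclusion.** The point holds in a limited form. Assessing complications is a stated aim, but section 2.5 has no outcome for bleeding, stenosis, infection, re-operation or device side effects. The swallowing, taste and pain measures cannot be compared between arms, because only TORS patients have them. Adverse events rest on passive capture in an open trial whose scheduled contact differs by arm. Any comparison of harm is therefore at risk of ascertainment bias.

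The size and direction of that bias cannot be determined from the document. The illustrative ratios, from 0.78 to 1.80, rest wholly on assumed capture of 50% to 90%. What is firm is the leverage of a single patient: 4 percentage points at 25 per arm. The primary AHI analysis is not affected. The change is worth making because the trial cannot otherwise properly meet an aim that it sets itself, and the remedy is cheap.

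**What to change.** 1. **Section 2.5:** add a secondary outcome giving, per arm, the number and proportion of patients with treatment complications from randomisation to 12 months, with 95% confidence intervals. Report each type separately: bleeding, stenosis, infection, dysphagia, unplanned re-admission or re-operation, and device side effects.
2. **Section 2.11:** keep the present rule and supplement it with one structured adverse-event enquiry, worded identically for both arms and made at the existing 3-, 6- and 12-month questionnaire and polygraphy contacts. It should ask about events treated at other hospitals, since the 24-hour duty is worded for events at the trial hospital.
3. **Section 2.6:** state which time points the control outpatient follow-ups refer to, and whether TORS patients have clinic visits at those times.

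If the full protocol already contains such an enquiry, steps 1 and 3 and a sentence describing it are enough.

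The cost is protocol wording, a short form and a few minutes per contact. More minor events will be recorded. No new visit or procedure is needed.
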